**4.2.- Study description**

The intention is to perform a single-centre interventional pilot study to evaluate the safety of administering intravenous rituximab as a rapid, ultrarapid or ultrarapid plus infusion in comparison with standard clinical practice at the standard rate of 400 mg/h.

**4.3.- Trial treatment, dose and treatment regimen**

In the case of patients assigned to the **rapid infusion group**, after the IV administration of premedication (generally dexchlorpheniramine 5 mg IV and paracetamol 1 g IV), the standard dose of rituximab (375 mg/m^2^ diluted in 250 ml of saline) will be administered over one hour, as follows: first 10 minutes at 450 mg/hour and subsequent 50 minutes at 730 mg/hour.

For the **ultrarapid infusion group**, after the administration of premedication (generally dexchlorpheniramine 5 mg IV and paracetamol 1 g IV), the standard dose of rituximab (375 mg/m^2^ diluted in 250 ml of saline) will be administered over half an hour, as follows: first 10 minutes at 450 mg/hour and subsequent 20 minutes at 1800 mg/hour.

And for the **ultrarapid plus infusion group**, after the administration of premedication (dexchlorpheniramine 4 mg orally and paracetamol 1 g orally), the standard dose of rituximab (375 mg/m^2^ diluted in 250 ml of saline) will be administered over half an hour, as follows: first 10 minutes at 450 mg/hour and subsequent 20 minutes at 1800 mg/hour.

**4.4.- Study duration**

12 months.

**4.5.- Biases and limitations of the study**

The pilot study proposed does not have a sufficient sample size to demonstrate statistically significant differences in the percentage of infusion-related reactions that may occur in each study group compared with the percentage of infusion-related reactions that occur in standard treatment with rituximab at the standard rate (i.e., 400 mg/h). However, as the maximum infusion rate described in the scientific literature is 60 min, the present study appears to be the first to evaluate the safety with ultrarapid infusion rates of 30 min. As such, despite lacking sufficient power, it has been decided to perform an initial pilot study to evaluate the safety of ultrarapid infusions before carrying out a subsequent multicentre clinical trial.

Given the escalation nature of the study, patients will not be assigned randomly to the three study groups and, if they do not suffer any adverse infusion-related reaction, the same patient may receive the infusions described for the three study groups. This may bias the results as the characteristics of the patient and the type of lymphoma they suffer may affect the percentage of infusion-related reactions that occur with each infusion type to be studied. However, and despite the small sample size, the intention is to analyse infusion-related reactions based on the characteristics of the disease.

# 5.- SUBJECT SCREENING AND WITHDRAWAL

Inclusion criteria:

- Patients who have tolerated the maximum intravenous administration rate for rituximab (400 mg/h) during the first or second infusion.
- The last infusion of rituximab must have taken place in the previous 3 months.
- All patients receiving rituximab may be included irrespective of whether they do so as monotherapy or in combination with chemotherapy and irrespective of the line in which they are receiving it.
- Patient in both induction and maintenance treatment will be included.
- All patients must sign the informed consent.

Exclusion criteria:

- Patients with an initial absolute lymphocyte count >10x10^3^ cells/µL.
- Patients who have presented hypersensitivity and serious adverse effects (grade 2 or higher) after the first or second infusion.
- Severe heart failure (NYHA class III-IV) or severe uncontrolled heart disease.
- Respiratory failure, uncontrolled COPD/severe asthma.
- Patients allergic to the premedication: paracetamol or polaramine.
- Severe active infection.
- Pregnant patients. *
- Refusal to participate

* For patients of child-bearing age (women of child-bearing age are considered to be those between menarche and post-menopause, except for those who are permanently sterile), a pregnancy test must be performed prior to treatment.

Women of child-bearing age participating in the trial must use effective contraceptive methods during treatment and for up to 12 months afterwards. These methods include:

- - - Sexual abstinence.
    - Female sterilisation.
    - Sterilisation of the (male) partner.
    - Intra-uterine device (IUD)

Withdrawal criteria:

- Onset of one or more grade 2 or higher infusion-related reactions
- The presence of four or more mild to moderate infusion-related reactions (25%) in the 16 patients of the corresponding cohort

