# 4.- TRIAL DESIGN

**4.1.- Variables**

Primary variable:

-Percentage of grade 2/3 or higher infusion-related reactions for the rapid, ultrarapid and ultrarapid plus infusions in comparison with the administration of rituximab as per standard clinical practice at the standard rate of 400 mg/h.

** Infusion-related reactions are defined as adverse events that occur in the first 24 hours after infusion of rituximab and which are considered to be related to infusion of the drug in the investigator's opinion.*

Secondary variables:

- Grade of infusion-related reactions (1-5 as per CTCAE version 4.0) occurring in each study group.

- Time (in minutes) between the start of infusion and onset of the infusion-related reaction.

Other variables:

- Age (years)

- Sex (male/female)

- Infusion group (rapid, ultrarapid or ultrarapid plus)

- Treatment type (induction/maintenance)

- Therapy type (rituximab in monotherapy/combination therapy - specify the type of concomitant treatment: chemotherapy, radiotherapy, targeted therapy, etc.)

- Lymphoma type (specify diagnosis)

- Rituximab cycle number

- Blood pressure, temperature, oxygen saturation and heart rate before starting and after finishing rituximab infusion

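### The reaction-history exclusion covers only the first or second infusion, yet maintenance and later-line patients are admitted, so a grade 2 or higher reaction at a later pre-study infusion does not bar entry

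*Protocol*

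**What the plan says.** All the entry criteria that bear on rituximab history are in Protocol section 5.

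- Tolerance (inclusion): "Patients who have tolerated the maximum intravenous administration rate for rituximab (400 mg/h) during the first or second infusion". The invitation text at the start of section 6 repeats this condition.
- Recency (inclusion): "The last infusion of rituximab must have taken place in the previous 3 months".
- Breadth (inclusion): "Patient in both induction and maintenance treatment will be included", and patients qualify "irrespective of the line in which they are receiving it".
- Reaction history (exclusion): "Patients who have presented hypersensitivity and serious adverse effects (grade 2 or higher) after the first or second infusion".

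Section 4.1 records "Rituximab cycle number" as a variable, and no upper limit on it is set for entry. Section 6 provides that one grade 2 or higher infusion-related reaction makes the cohort unsafe and suspends the trial. Each cohort has 16 infusions.

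**The concern.** The breadth criteria admit patients who may be well past their second infusion, while the history criteria stop at the second. A reaction at the third or a later infusion before study entry falls between the two.

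Two things are at stake. First, a patient already known to have reacted could be given an infusion faster than 400 mg/h in what section 4.5 describes as apparently the first evaluation of 30-minute infusion. Second, the hypothesis in section 3.1 is about infusion rate, and the tolerance criterion is there to restrict the study to people who tolerate 400 mg/h. If a known late reactor enters and reacts again, the single-event rule suspends the trial, and nobody can say whether the rate or the patient's own history was responsible.

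**Working it through.** The point turns on wording, and the plan has no figure to reproduce. I took a hypothetical patient through the list: 400 mg/h tolerated at infusions 1 and 2, a grade 2 or higher reaction at infusion 5 before the study, last infusion within the past 3 months, now in late induction or maintenance.

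1. Tolerance criterion: met at the first or second infusion. Nothing is asked about later ones.
2. Recency criterion: met. It fixes when the last infusion took place, not whether it was free of a reaction.
3. Phase and line of treatment: both phases and every line are admitted.
4. Reaction exclusion: the reaction at infusion 5 did not follow infusion 1 or 2, so it is not caught.
5. Remaining exclusions (lymphocyte count, cardiac and respiratory disease, allergy to the premedication, active infection, pregnancy, refusal): none refers to a reaction to rituximab.
6. Section 6: entry depends on the section 5 lists and adds no further history condition.

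The patient is therefore eligible as written.

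**Illustration of leverage.** The documents give no risk per infusion, so every risk below is my assumption, as is independence between infusions. Let p be the risk of a grade 2 or higher reaction in a tolerant patient and r the risk in a prior late reactor. With k such patients among 16 infusions, the probability of at least one event is 1 − (1 − p)^(16 − k) × (1 − r)^k. Take p = 1%.

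| Prior late reactors (k) | r = 10% | r = 20% | r = 30% |
| --- | --- | --- | --- |
| 1: 1 − 0.99^15 × (1 − r) | 22.6% | 31.2% | 39.8% |
| 2: 1 − 0.99^14 × (1 − r)^2 | 29.6% | 44.4% | 57.4% |

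With no such patient the figure is 1 − 0.99^16 = 14.9%. The table shows how much one patient can weigh under a single-event rule. It does not estimate what will happen in this trial.

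**The case against.** **The wording may be looser than I take it to be.** The exclusion could mean any time from the first or second infusion onwards. That reading is possible, but the inclusion criterion uses the parallel phrase with 'during', which fixes the same two infusions and favours the narrow sense. If both readings are open, the criterion still needs clarifying.

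**Such patients may hardly exist.** Section 2.1 says that since 2010 patients at this hospital who tolerate 400 mg/h at the first infusion start later ones at that rate, with no significant complications reported. It adds that no infusion-related complications have been seen at 400 mg/h. In a single-centre study this bears directly on the size of the problem, and it stands: few patients are likely to fall into the gap. The statements are qualitative, however, and do not close it.

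**The numbers are assumed.** This also stands. The arithmetic is right, but the risks and the count of prior reactors come from no document.

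**A stronger reading, about re-entry.** A reader might infer that the gap also lets a patient who reacted in one study cohort enter the next. The documents do not support this for grade 2 or higher reactions. Section 4.5 allows further infusions only on a condition: "if they do not suffer any adverse infusion-related reaction, the same patient may receive the infusions described for the three study groups". Section 5 makes this a withdrawal criterion: "Onset of one or more grade 2 or higher infusion-related reactions". Section 6 then suspends the trial, so no later cohort would be open. For grade 1, section 4.5 sets a stricter condition for a different situation, which does not contradict the entry list. It follows that the cohorts cannot be said to differ in population because of this wording.

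Nor do the documents say that a study infusion is usually the third or later. A patient who tolerated 400 mg/h at the first infusion could have the second as a study infusion. The point needs only that later entry is allowed, which it is.

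**Conclusion.** The point holds for reactions before study entry and no further. As written, section 5 does not bar a patient whose grade 2 or higher reaction came at the third or a later pre-study infusion, and no other section does so. This rests on the narrow reading of the exclusion, which the parallel inclusion wording supports, and on maintenance and later-line patients being able to enter with more than two infusions behind them, which the list permits.

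The number of patients affected is probably small, given the site's account, and cannot be quantified from the documents. The consequence of one such patient is nonetheless large, because a single event suspends the trial. The criterion should be amended. The gap does not by itself invalidate the design, and it says nothing against the separate handling of patients who react on study.

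**What to change.** Reconcile the reaction-history exclusion in section 5 with the admission of maintenance and later-line patients. Its look-back should match the infusions that admitted patients may already have had, and the grade limit should stay as the Protocol states it. The amendment should also remove the doubt over what 'after' means.

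This takes one sentence in the eligibility list. It changes neither sample size nor analysis. A few otherwise eligible patients may be lost, and on the site's own account that number should be low.

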# 6.- SUBJECT TREATMENT

When the patient attends the haematology surgery and has tolerated the maximum intravenous administration rate for rituximab (400 mg/h) during the first or second infusion, they will be invited to participate in the study and will be given the informed consent. If the patient complies with all the inclusion criteria and none of the exclusion criteria, and decides to participate, they will be given an appointment to attend the day hospital for administration of their treatment cycle at the infusion rate being studied at that time.

Three successive intervention groups with different infusion rates (rapid, ultrarapid and ultrarapid plus) will be established. The procedure for each cohort will be considered to be safe if fewer than four mild to moderate infusion-related reactions occur in the 16 patients from the corresponding cohort (25% of reactions). The onset of one or more grade 2 or higher infusion-related reactions will imply that the cohort is not safe and the clinical trial will be suspended. Before commencing the next cohort, a haematology specialist not linked to Araba University Hospital Haematology Department will carry out a safety monitoring. This will involve an evaluation of all infusions performed, with access to the progress reports (medical and nursing) to determine whether a reaction has occurred and the grade thereof. In an attempt to minimise the influence of the investigator on the safety evaluation, the safety monitor will receive the progress reports after references to the grade of the infusion-related reaction contained in the electronic medical records have been censored.

Rituximab will be diluted in 250 mL provided the maximum concentration established in the summary of product characteristics (max. 4 mg/mL) is not exceeded. The rituximab dose will not be changed.

If the patient is receiving concomitant chemotherapy, this will be administered after rituximab once the absence of adverse reactions has been confirmed.

The interventions applied in each of the three study groups are described below:

RAPID INFUSION GROUP

Administration of the IV premedication half an hour prior to the infusion of rituximab as per the standard regimen; generally, dexchlorpheniramine 5 mg IV and paracetamol 1 g IV half an hour prior to rituximab.

The rituximab dose will then be administered at the standard dose: 375 mg/m^2^ diluted in 250 mL of saline over one hour, as follows:

- - - First 10 minutes at 450 mg/hour
    - Subsequent 50 minutes at 720 mg/hour

A total of 16 infusions will be included in this group and the safety thereof will be evaluated. If the number of AEs is not higher than normal (more than three infusion-related reactions), the second intervention will commence. In the event that the number of infusion-related reactions is higher than in standard clinical practice, the study will be suspended without continuing with the following groups.

ULTRARAPID INFUSION GROUP

Administration of the IV premedication half an hour prior to the infusion of rituximab as per the standard regimen; generally, dexchlorpheniramine 5 mg IV and paracetamol 1 g IV half an hour prior to rituximab.

The rituximab dose will then be administered at the standard dose: 375 mg/m^2^ diluted in 250 mL of saline over half an hour, as follows:

- - - First 10 minutes at 450 mg/hour.
    - Subsequent 20 minutes at 1800 mg/hour.

A total of 16 infusions will be included in this group and the safety thereof will be evaluated. If the number of infusion-related reactions is not higher than normal (more than three infusion-related reactions), the third intervention will commence. In the event that the number of infusion-related reactions is higher than in standard clinical practice, the study will be suspended without continuing with the following group.

ULTRARAPID PLUS INFUSION GROUP

Administration of the oral premedication half an hour prior to the infusion of rituximab as per the standard regimen for administration of subcutaneous rituximab: dexchlorpheniramine 4 mg orally and paracetamol 1 g orally half an hour prior to rituximab.

The rituximab dose will then be administered at the standard dose: 375 mg/m^2^ diluted in 250 mL of saline over half an hour, as follows:

- - - First 10 minutes at 450 mg/hour.
    - Subsequent 20 minutes at 1800 mg/hour.

A total of 16 infusions will be included in this group and the safety thereof will be evaluated. This ultrarapid infusion regimen will be considered to be safe if the number of infusion-related reactions is three or less.

Safety will be evaluated by monitoring infusion-related reactions, including all haematological and non-haematological serious and non-serious adverse events related to the study drugs. If an infusion-related reaction occurs, the standard administration rate of 400 mg/h will be used.

To that end, vital signs (temperature, blood pressure, heart rate and oxygen saturation) will be monitored every 10 minutes and all events that occur will be recorded in the CRF. At 24 hours post-infusion, the study nurse will contact the patient by telephone to determine whether any adverse reaction has occurred.

The other evaluations to be performed during the study are the same as those in standard clinical practice. Diagnostic tests and the pharmacological treatment will be carried out irrespective of participation of the patient in the study.

Study diagram:

[figure not shown]

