# 8.- STATISTICS

## 8.1.- Sample Size

The expected number of infusions is 48, distributed into 16 infusions per group. It is recommended to include between 30 and 50 measurements in a pilot study^18,19^.

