## 8.2.- Statistical analysis

A general description of all study variables will be performed. Qualitative variables will be expressed as absolute frequencies and percentages, and quantitative variables as the mean and standard deviation (median and 25th and 75th percentiles if they do not follow a normal distribution). The primary endpoint will be evaluated using a chi-squared test (with a Fisher correction if it does not comply with the criteria) and the secondary endpoints will be evaluated by performing a chi-squared test (with a Fisher correction if they do not comply with the criteria) for categorical variables, and Student’s t-test (or Mann–Whitney U-test if they do not follow a normal distribution) will be applied for continuous variables. A Kaplan Meier survival analysis will be applied to determine the time to the infusion-related reaction. A statistical significance level of p<0.05 will be used in all tests. Statistical analysis will be performed using the statistical software packages R (version 3.5.0) and SPSS (version 23.0).

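### A cohort is called safe on a raw count of three or fewer reactions in 16 with no upper bound; the count alone passes a true 25% rate up to 40.5% of the time

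*Protocol*

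**What the plan says.** Section 6 states the rule for every cohort: "The procedure for each cohort will be considered to be safe if fewer than four mild to moderate infusion-related reactions occur in the 16 patients". It glosses the count as 25%. The next sentence adds a second condition: "The onset of one or more grade 2 or higher infusion-related reactions will imply that the cohort is not safe", and the trial is then suspended.

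Section 5 repeats both conditions as withdrawal criteria, the first as "The presence of four or more mild to moderate infusion-related reactions (25%) in the 16 patients of the corresponding cohort".

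For the last cohort (ultrarapid plus), section 6 restates the rule as a count only: "This ultrarapid infusion regimen will be considered to be safe if the number of infusion-related reactions is three or less". No further cohort follows it.

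Section 8.1 fixes the numbers: "The expected number of infusions is 48, distributed into 16 infusions per group". Section 8.2 sets a significance level ("A statistical significance level of p<0.05 will be used in all tests"), but the count rule is not one of those tests, and no interval, tolerable true rate or error rate is attached to it.

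Section 4.5 concedes limited size, in these terms: "The pilot study proposed does not have a sufficient sample size to demonstrate statistically significant differences in the percentage of infusion-related reactions".

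**The concern.** One count does two jobs. As a gate for opening the next cohort, three or fewer of 16 is a judgement that a pilot is entitled to make. As a conclusion that a regimen is safe, it is a statement about the regimen's underlying reaction rate, and an observed proportion in 16 infusions does not support such a statement without a bound. The two roles separate most clearly in the ultrarapid plus cohort, where the count gates nothing and the label is the result.

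Section 4.5 places this pilot ahead of a multicentre trial. A label of safe that treats 0, 1, 2 and 3 of 16 alike would go into that trial's rationale without showing how high the true rate could be.

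**Working it through.** **Inputs.** n = 16 per cohort (sections 6 and 8.1). The count condition is met if X ≤ 3 (section 6). The grade condition fails the cohort on any reaction of grade 2 or higher (sections 5 and 6). The protocol gives no grade split, so the shares used in step 3 are assumptions. Infusions are taken as independent, each with at most one counted reaction.

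**1. The plan's own figures.** 4/16 = 25% and 3 × 16 = 48 infusions; both reproduce. The largest passing proportion is 3/16 = 18.75%.

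**2. Count condition alone.** P(X ≤ 3) = Σ over x = 0 to 3 of C(16,x) p^x (1−p)^(16−x). At p = 0.25 the four terms are 0.0100 + 0.0535 + 0.1336 + 0.2079 = 0.405.

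| True rate | P(3 or fewer of 16) |
|---|---|
| 10% | 93.2% |
| 15% | 79.0% |
| 20% | 59.8% |
| 25% | 40.5% |
| 30% | 24.6% |
| 40% | 6.5% |

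**3. Both conditions together.** Let the total rate be p = 0.25 and let a share s of reactions be grade 2 or higher, so the grade 1 rate is g = 0.25(1−s). The cohort passes with no grade 2 or higher reaction and at most three of grade 1: Σ over x = 0 to 3 of C(16,x) g^x (0.75)^(16−x).

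| Assumed share s | P(called safe) at a 25% total rate |
|---|---|
| 0% | 40.5% |
| 5% | 36.0% |
| 10% | 31.8% |
| 25% | 21.3% |
| 50% | 9.6% |

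So 40.5% is the ceiling. It is reached when all reactions are grade 1, or when the count-only sentence for the last cohort is applied as it stands.

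**4. What each passing result leaves open.** The one-sided 95% exact (Clopper–Pearson) upper limit is the 0.95 quantile of Beta(x+1, 16−x).

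| Observed | Upper limit |
|---|---|
| 0/16 | 17.1% |
| 1/16 | 26.4% |
| 2/16 | 34.4% |
| 3/16 | 41.7% |

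For 0/16 this is 1 − 0.05^(1/16) = 0.171. These limits need no assumption about the grade split. All four results earn the same label.

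**5. Grade wording.** In the table of section 3.2.1 moderate is grade II. The count condition speaks of mild to moderate reactions and so admits up to three that could include grade 2. The following sentence fails the cohort on a single grade 2 reaction. The two cannot both apply as written.

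**The case against.** A reader might infer that a regimen at a true 25% rate is simply declared safe about 40% of the time. The documents do not support that for the full rule: the grade condition belongs to the same verdict and can only lower the figure. Under it a cohort passes only with 0/16 at grade 2 or higher, which is the category the primary variable uses, and the one to three tolerated reactions must be grade 1, which section 3.2.1 describes as transitory and needing no intervention. This stands and limits the size of the point.

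A reader might also infer that 25% is the protocol's maximum acceptable true rate, that 40.5% is therefore a miss rate, and that safe should be concluded only when the upper limit is below 25%. That also fails. The 25% is only the observed cut-off 4/16, and section 6 elsewhere describes the same count as exceeding what is normal. A formal test against 25% would bring in a threshold the protocol never set. It would also be harsh: only 0/16 would pass, and at a true rate of 5% that occurs in just 0.95^16 = 44% of cohorts.

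Nor is 40.5% the chance that the whole programme passes. The cohorts are successive; at 25% in all three, with independence, the count alone passes all of them with probability 0.405³ = 6.6%.

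Two defences carry less weight. The admission of low power in section 4.5 concerns the comparison with 400 mg/h; it does not qualify the word safe and argues against using it. An analysis plan could add intervals, but the verdict and its wording are fixed in section 6 of the protocol and would remain. The independent haematologist's review checks whether reactions occurred and their grade; it adds no precision.

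**Conclusion.** The point holds in a limited form. The protocol attaches a safety conclusion to a raw count in 16 infusions with no upper bound. The count alone passes a true 25% rate 40.5% of the time, the maximum for the full rule. With an assumed 10% or 25% of reactions at grade 2 or higher it is 31.8% or 21.3%. Whatever the grade split, 3/16 does not exclude a true rate up to 41.7%, and even a cohort with no grade 2 or higher reaction does not exclude a rate of such reactions up to 17.1%. The label therefore overstates the evidence, most plainly in the last cohort.

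The figures assume independent infusions. Section 6 alternates between 16 patients and 16 infusions, and section 4.5 says "the same patient may receive the infusions described for the three study groups". Repeat infusions in one patient within a cohort would make the binomial figures approximate. The counts themselves are not criticised as gates.

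**What to change.** Leave all escalation and suspension counts unchanged, and separate them from the conclusion.

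- In section 6, replace the statement that a cohort is considered safe with 'the escalation criterion is met'. For the ultrarapid plus cohort, use 'the prespecified count criterion is met'.
- In section 8.2 add: 'For each cohort, the proportion of infusions with any infusion-related reaction and the proportion with a grade 2 or higher reaction are reported, each with its one-sided 95% exact upper limit. Statements about safety are based on these limits.'
- Beside the rule, state that three or fewer reactions in 16 occur with up to 40% probability at a true rate of 25%.
- Reconcile the mild-to-moderate count with the grade 2 suspension condition in sections 5 and 6, and with the count-only sentence for the last cohort. Which reading applies is for the investigators to settle.

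The cost is wording in sections 5, 6 and 8.2 and two exact limits per cohort, with no extra patients or visits. The relabelling and the limits leave patient management as it is. The drawback is a less favourable label for cohorts with one to three reactions, which would be reported with upper limits of 26.4% to 41.7% instead of as safe.

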## 3.2 Study population

**3.2.1- PRIMARY ENDPOINT**

To evaluate the safety of a rapid, ultrarapid and ultrarapid plus infusion of rituximab based on the percentage of grade 2/3 or higher infusion-related reactions in comparison with the administration of rituximab as per standard clinical practice at the standard rate of 400 mg/h.

Infusion-related reactions are defined as adverse events that occur in the first 24 hours after infusion of rituximab and which are considered to be related to infusion of the drug in the investigator's opinion.

Infusion-related reactions will be graded as the EORTC guidelines: Common Terminology Criteria for Adverse Events (CTCAE) Version 5.0 of EORTC (27 November 2017)

| **GRADE** | **REACTION** |
| --- | --- |
| Grade I: Mild | - - Transitory reaction   - Infusion not suspended   - No indication for intervention |
| Grade II: Moderate | - - Infusion suspended, with rapid recovery of symptoms after symptomatic treatment (e.g., antihistamines, NSAIDs, analgesia, volume support)   - Prophylactic medication for less than 24 hours |
| Grade III: Severe | - - Prolonged symptoms (e.g., slow response to symptomatic medication or suspension of infusion)   - Symptoms recur after initial improvement   - Hospitalisation indicated |
| Grade IV: Very severe | - - Life-threatening symptoms   - Urgent intervention indicated |
| Grade V: | - - Related death |

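### The cohort safety rule contradicts itself: three or fewer reactions with at least one Grade II make a cohort both safe and not safe

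*Protocol*

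**What the plan says.** Section 6 of the protocol (Subject treatment) gives two criteria in consecutive sentences. A cohort's procedure "will be considered to be safe if fewer than four mild to moderate infusion-related reactions occur" among its 16 patients. The sentence after it says that "one or more grade 2 or higher infusion-related reactions will imply that the cohort is not safe and the clinical trial will be suspended".

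The grading table in section 3.2.1, the only scale the protocol gives for infusion-related reactions, has mild for Grade I and "Grade II: Moderate" for the next level.

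The withdrawal criteria in section 5 list the same two thresholds: "Onset of one or more grade 2 or higher infusion-related reactions" and "The presence of four or more mild to moderate infusion-related reactions (25%) in the 16 patients of the corresponding cohort".

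Later in section 6 each infusion group has its own gate, based on a count of three. For the ultrarapid group: "If the number of infusion-related reactions is not higher than normal (more than three infusion-related reactions), the third intervention will commence". The ultrarapid plus regimen "will be considered to be safe if the number of infusion-related reactions is three or less". The rapid group's gate uses the same count. None of the three mentions grade or points back to the grade 2 rule.

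**The concern.** On the protocol's own scale, mild to moderate means Grade I to Grade II. The count rule therefore tolerates up to three Grade II reactions, and the grade rule tolerates none. A cohort with one to three reactions, at least one of them Grade II and none higher, gets opposite verdicts from adjacent sentences.

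What is at stake is the trial's main decision: whether to move to the next, faster or less heavily premedicated cohort, whether to suspend the trial, and whether to call the last regimen safe. In the section 3.2.1 table, a Grade II reaction means that the infusion was interrupted and symptoms were treated. Section 4.5 presents the study as apparently the first to assess 30-minute infusions, so such a reaction should not leave room for a choice of rule after the event.

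The outside haematologist who reviews each cohort does not close the gap. Section 6 asks that person to establish whether a reaction occurred and its grade, not which threshold governs.

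**Working it through.** **Inputs from the protocol.** Cohort size n = 16 infusions (section 6; section 8.1 gives 48 in total). Count rule: safe with 0 to 3 reactions. Grade rule: not safe with 1 or more reactions of grade 2 or higher. Grade I is mild and Grade II moderate (section 3.2.1).

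**The protocol's own figures.** 4/16 = 25% and 3 × 16 = 48. Both reproduce.

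**Outcomes in conflict.** Let a be the number of Grade I and b the number of Grade II reactions, with none higher. There are 10 pairs with a + b ≤ 3. Four have b = 0 (a = 0, 1, 2, 3), and both rules call them safe. The other six, (0,1), (1,1), (2,1), (0,2), (1,2) and (0,3), are safe by the count and not safe by the grade rule.

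**How often this could happen.** The protocol states no reaction rates, so the rates below are assumptions: g1 = Grade I rate and g2 = Grade II rate per infusion, no Grade III or higher, 16 independent infusions, all completed.

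- Safe by the count: C = P(Bin(16, g1 + g2) ≤ 3)
- Safe if the grade rule governs as well: S = (1 − g2)^16 × P(Bin(16, g1/(1 − g2)) ≤ 3)
- Conflict: C − S
- At least one Grade II: A = 1 − (1 − g2)^16
- Share of those cohorts that the count still calls safe: (C − S)/A

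For g1 = 5%, g2 = 2%: C = P(Bin(16, 0.07) ≤ 3) = 0.978. S = 0.98^16 × P(Bin(16, 0.0510) ≤ 3) = 0.7238 × 0.9925 = 0.718. Conflict = 0.9779 − 0.7184 = 0.260. A = 1 − 0.7238 = 0.276. Share = 0.2595/0.2762 = 0.94.

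| Grade I / Grade II rate (assumed) | Safe by count, C | Safe if grade rule governs, S | Conflict, C − S | At least one Grade II, A | Share still called safe by count |
| --- | --- | --- | --- | --- | --- |
| 3% / 0.5% | 0.998 | 0.922 | 0.076 | 0.077 | 99% |
| 5% / 2% | 0.978 | 0.718 | 0.260 | 0.276 | 94% |
| 10% / 5% | 0.790 | 0.405 | 0.385 | 0.560 | 69% |
| 10% / 10% | 0.598 | 0.168 | 0.430 | 0.815 | 53% |

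Over a grid of Grade I rates of 5%, 10% and 15% and Grade II rates from 1% to 10%, the conflict probability runs from about 0.09 (15%/1%) to 0.61 (5%/10%).

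**The case against.** The strongest defence is that the two thresholds are separate triggers and either one stops the trial. The section 5 list reads naturally that way: one Grade II reaction meets the first criterion, and not meeting the second clears nothing. Timing supports it too, since the grade rule acts at onset and the count is a verdict on a full cohort, so a Grade II reaction before the last infusion would suspend the trial before the count was complete. This is a plausible reading and may well be what was meant. But the visible text does not state it, and the study diagram cannot be seen. It also leaves the reference to moderate reactions without effect, because one such reaction would already have stopped the trial. And it does not repair the three group gates, which read literally would pass a cohort with a Grade III reaction.

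A second defence is that *moderate* belongs to the general adverse event scale in section 7, which goes by effect on daily activity. A reaction could be moderate there and Grade I in section 3.2.1. That narrows the overlap but does not remove it: the section 7 scale is not tied to the cohort rule, and a reaction moderate on that scale can still be Grade II.

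The probabilities are open to the charge of high assumed rates. Patients must have tolerated 400 mg/h, those with grade 2 or higher effects at the first or second infusion are excluded, and section 2.1 reports no significant complications since the site began giving later infusions at 400 mg/h. That is fair, although the protocol offers no experience with 30-minute infusions. At 3%/0.5% the conflict probability falls to 0.076. The suspension rule would also often stop a cohort before 16 infusions, which the calculation ignores. These points affect the size of the problem, not the contradiction.

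**Conclusion.** The concern holds. As written, six of the ten possible outcomes with three or fewer reactions and none above Grade II are both safe and not safe, and the group gates side with the count. This follows from the text alone and needs no assumption about rates.

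How often it would matter does depend on assumed rates: from 0.076 per cohort at 3%/0.5% to 0.430 at 10%/10% in the table, and up to 0.61 on the wider grid. When at least one Grade II reaction occurs and none is higher, the count would still pass 53% to 99% of cohorts in the tabulated scenarios. The point must be fixed before enrolment because the rule controls escalation, suspension and the final safety label.

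**What to change.** State one rule, in CTCAE grades. The default should be the cautious threshold already in section 6: any infusion-related reaction of Grade II or higher makes the cohort not safe and suspends the trial, and four or more Grade I reactions in 16 also make the cohort not safe. This fits the section 5 exclusion of "Patients who have presented hypersensitivity and serious adverse effects (grade 2 or higher) after the first or second infusion".

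In sections 5 and 6, replace the mild-to-moderate wording of the count rule with Grade I. Have the gates for the rapid, ultrarapid and ultrarapid plus groups refer to this single rule instead of restating a count.

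If the sponsor does intend to tolerate Grade II reactions, it should instead raise the suspension trigger to Grade III in both sections and say so before enrolment. Under the default rule and the assumed rates, a cohort is declared safe with the probabilities in the column for S.

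The cost is a protocol wording amendment, with no extra patients or procedures.
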